After assessing the baseline measures, all eligible participants will be randomly assigned to an intervention or waiting control group upon completion of the initial CATI (*t*_*0*_). The allocation (stratified by location) will take place automatically with a 1:1 ratio in an alternating fashion. The first participant who successfully completes the CATI will be allocated to the intervention group; the second participant will be allocated to the waiting control group, and so on. Because allocation is carried out in “real-time”, there is no predetermined list. Hence, whether a participant is allocated to the intervention or control group is not known in advance. Moreover, because at any point in time more than one CATI will be conducted simultaneously, interviewers cannot predict the allocation of a given participant prior to the end of the current interview. The information about the group to which participants will be assigned is only revealed to the interviewers by the time the interview is completed.

Upon completion of the CATI, interviewers will invite participants who are assigned to the intervention group to complete JOBS Program Germany, usually within two weeks. Participants who are assigned to the intervention group might immediately decline participation in the program. The respective persons are then assigned to a separate (waiting control) group and their place in the intervention group is filled with another participant who has not yet been allocated to either group. Any such deviation from the randomly allocated intervention will be recorded in the methods reports and in the dataset. Participants in the waiting control group will be told that JOBS Program Germany will start in 6 months Participants who are randomly allocated to the waiting control group cannot participate in JOBS Program Germany, meaning that it is not possible for participants to self-select into the intervention group.

Participants in the waiting control group are not allowed to join JOBS Program Germany during the 6 months of the trial. However, participants in both the intervention and waiting control group will not actively be discouraged or otherwise prevented from participating in any employment promotion measures of the Federal Employment Agency or any prevention or health promotion measures of their choice other than the JOBS Program Germany. Participation in the intervention is voluntary and may be terminated by the participants at any time.

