### Sample size

This trial is conceptualized as a confirmatory study. The respective studies in the US and Finland reported small effect sizes (Cohen’s *d*) ranging from about .14 to .32. for self-esteem, self-efficacy, psychological distress, and depressive symptoms [7, 11]. In order to detect effect sizes of .2, which we deem to be of practical relevance, with 85% power and the conventional alpha-level of .05 (two-tailed t-test), we require a sample size of 450 persons per group. This sample size also allows us to detect a 10 percentage points difference in reemployment with 85% power and alpha-level of .05, assuming a reemployment rate of 30% in the waiting control group. To arrive at our target sample size, we aim at recruiting a total of 1500 unemployed, assuming a dropout rate of 60% between the pre-test (*t*_*0*_) and the 6-months follow-up (*t*_*2*_). We further expect about 60% of the unemployed who attend the information event to participate in our study, resulting in an estimated 2500 unemployed who attend an information event. We summarize our assumptions about response rates and panel attrition in Table 1.

**Table 1 Tab1:** Assumptions about number of participants, response rates, and panel attrition

	Information Event	Allocation/Pre-Test	Post-Test	6-months follow-up
	*-t*_*1*_	*t*_*0*_	*t*_*1*_	*t*_*2*_
Response rate (per cent)		60%	80%	75%
Intervention group (n)	2500	750	600	450
Waiting control group (n)		750	600	450
Total (n)	2500	1500	1200	900

Notes: -*t*_*1*_: 4–5 weeks before JOBS Program Germany; *t*_*0*_: pre-test interview and randomization within 1–2 weeks before JOBS Program Germany; *t*_*1*_: post-test interview within 4 weeks after JOBS Program Germany; *t*_*2*_: second post-test interview (follow-up) 6 months after JOBS Program Germany

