### Statistical methods

Statistical methods will include t-tests (or equivalent tests for proportions) as well as linear and (binary) logistic regression models. We will compare primary and secondary outcomes between the intervention and waiting control groups.

Reintegration into the labor market (employed vs. unemployed) and the type of contract (temporary vs. permanent) will be assessed using t-tests (or equivalent test of proportions) and logistic regression models. In all analyses, we will treat Likert-Type items as continuous variables. For life-satisfaction, depressive symptoms, and psychological distress, we will first construct (additive) indices. We will then test mean differences in the respective indices between intervention and waiting control groups using t-tests. In multivariate analyses, we will use linear regression models to adjust for baseline-measures of the respective outcomes. Additional models will also adjust for socio-demographic characteristics and indicators of labor market biography, such as the duration of unemployment. We proceed in a similar fashion to analyze self-esteem, self-efficacy and our secondary outcomes job satisfaction and job-search intensity.

To test for potential effect modifications, we include interaction terms between our treatment-indicator and the respective moderators (job-search intensity, duration of unemployment) in the respective regression models.

All multivariate analyses will include controls for socio-demographic variables and (un-)employment history. We will repeat our main analyses stratified by gender. All analyses will be carried out according to the  “intention-to-treat” principle. Participants will be treated as belonging to the group to which they were originally (randomly) allocated. We tolerate low proportions of missing values of up to 5%, and perform listwise-deletion (complete-case analyses). If the proportion of missing values exceeds the predefined threshold of 5%, we will treat missing values by means of multiple imputation [31–33].

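### Neither the t-test nor the regression is named as deciding for each index outcome, the two covariate sentences conflict, and location, the allocation stratum, is in no listed model

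*Protocol article*

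**What the plan says.** The Procedure section fixes the design: "The allocation (stratified by location") and 1:1, by alternation, after the t0 interview has recorded the baseline measures.

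The Statistical methods section then describes these comparisons:

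- For the indices (life satisfaction, depressive symptoms, psychological distress): "We will then test mean differences in the respective indices between intervention and waiting control groups using t-tests". The next sentence plans linear regression that takes account of the t0 value of the same outcome. Self-esteem, self-efficacy and the secondary outcomes follow a similar path.
- After that regression: "Additional models will also adjust for socio-demographic characteristics and indicators of labor market biography".
- Two paragraphs on: "All multivariate analyses will include controls for socio-demographic variables and (un-)employment history".
- For reemployment and contract type: a t-test or test of proportions, and logistic regression.

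The section also promises to repeat the main analyses by gender, without saying which analyses are the main ones. The Interim analyses section applies the same methods at t1. Location appears in none of these descriptions.

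The Sample size section plans on the unadjusted test: "with 85% power and the conventional alpha-level of .05 (two-tailed t-test), we require a sample size of 450 persons per group".

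**The concern.** Three things do not fit together.

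1. **No deciding analysis.** The trial calls itself confirmatory, yet each index hypothesis has at least two planned p-values, one unadjusted and one adjusted, with no ranking. They can fall on opposite sides of 0.05. The reader then cannot tell which one answers the hypothesis, and the more favourable could be put forward.

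2. **Conflicting covariate sentences.** If socio-demographic variables enter only in further models, there is a regression adjusted for baseline alone. If every multivariable model contains them, there is not. Whether an index has two analyses or three depends on which sentence governs.

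3. **Design and analysis differ on location.** Allocation is balanced within location, and location may well carry local labour-market differences. The section names its adjustment variables, and location is not among them.

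At stake are a clear confirmatory result and precision that the collected data already allow.

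**Working it through.** **Inputs from the Sample size section.** Two-sided alpha 0.05 and power 85% ("with 85% power and the conventional alpha-level of .05 (two-tailed t-test"); d = 0.2 ("In order to detect effect sizes of .2, which we deem to be of practical relevance"); 450 analysed per group, which is also the 6-month figure in Table 1. For reemployment, the section gives this target: "detect a 10 percentage points difference in reemployment with 85% power and alpha-level of .05, assuming a reemployment rate of 30% in the waiting control".

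**Inputs assumed here.** The protocol gives neither the baseline-to-follow-up correlation r nor the share of outcome variance between locations (ICC). I use r = 0.3-0.7 and ICC = 0.01-0.10.

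**Step 1: the plan's own figure.** n per group = 2(1.960 + 1.036)² / 0.2² = 449 by the normal approximation, and 449.9, so 450, by the exact t calculation. With 450 per group the standard error is √(2/450) = 0.0667 and 0.2/0.0667 = 3.0, so power = Φ(3.0 − 1.96) = 0.851. The stated 450 is reproduced. For 30% against 40%, 407 per group are needed (427 with continuity correction), and 450 gives 88.3% power, so that statement is also met.

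**Step 2: t-test against baseline-adjusted regression.** Adjustment multiplies the residual variance by 1 − r², so power = Φ(3.0/√(1 − r²) − 1.96). The required n per group is 449 × (1 − r²), rounded up.

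| r (assumed) | Power at 450 per group | n per group for 85% |
|---|---|---|
| t-test, no adjustment | 0.8508 | 449 |
| 0.3 | 0.8820 | 409 |
| 0.4 | 0.9055 | 378 |
| 0.5 | 0.9337 | 337 |
| 0.6 | 0.9633 | 288 |
| 0.7 | 0.9875 | 229 |

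Both analyses are already planned, so the table shows the gap between them. It does not show a loss that is built into the plan.

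**Step 3: leaving out location.** With arms balanced within location, the true variance of the difference carries the factor 1 − ICC, while the t-test uses the full variance. Then:

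- true alpha = 2[1 − Φ(1.96/√(1 − ICC))]
- power without location = Φ((3.0 − 1.96)/√(1 − ICC))
- power with location = Φ(3.0/√(1 − ICC) − 1.96)

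| ICC (assumed) | True alpha | Power without location | Power with location |
|---|---|---|---|
| 0.01 | 0.0489 | 0.8521 | 0.8543 |
| 0.02 | 0.0477 | 0.8533 | 0.8578 |
| 0.05 | 0.0443 | 0.8570 | 0.8682 |
| 0.10 | 0.0388 | 0.8635 | 0.8854 |

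The loss runs from 0.2 points (0.8543 − 0.8521) to 2.2 points (0.8854 − 0.8635).

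**Step 4: both adjustments.** With r = 0.5 and ICC = 0.05 the variance factor is 0.75 × 0.95 and power is 0.9445.

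**The case against.** The strongest reply is that the plan already contains the better analysis. A reader who stops at the t-test sentence might infer that the baseline score is thrown away; the very next sentence adjusts for it. A reader might also infer that the t-test is the lead analysis, because it comes first and the sample size rests on it. No sentence says so, and the absence of any ranking is the actual defect.

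Nor is sizing on the t-test an error. It is the least precise of the planned analyses, so the calculation is conservative.

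Omitting location might be read as invalidating the standard errors. Under balance within location they are too large, not too small, so the test is slightly conservative and no bias follows. Whether a model carries a location term is also detail that an article may leave to a fuller protocol or analysis plan, so its absence alone would be thin ground.

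Finally, a count of three competing analyses for every outcome goes too far. Reemployment has a test of proportions and logistic regression, and everyone is unemployed at t0, so there is no informative baseline value. For the indices the count depends on which covariate sentence governs.

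All of this stands. It does not answer two points in the article's own text: parallel tests with none named as deciding, and two covariate sentences that cannot both hold. The location remark remains as a minor point of efficiency, because the article does list its adjustment variables.

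**Conclusion.** The point holds as one of clarity and efficiency; it does not threaten validity. The deciding analysis for each index outcome is open, and the adjustment set is stated in two incompatible ways. If the t-test decides, power for d = 0.2 is 85%; if the baseline-adjusted regression decides, it is about 88-99% for r between 0.3 and 0.7. Omitting location costs roughly 0.2-2 points of power and brings true alpha to about 0.049-0.039 for an ICC of 0.01-0.10, with no inflation of type I error.

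These sizes rest on assumed r and ICC and on 450 analysed per group. The location figures also assume balance within location, which attrition would weaken, and they do not model clustering by training group. The requirement of 450 per group stands.

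**What to change.** - **Continuous outcomes.** Name one primary analysis for each: linear regression of the t2 score on arm, t0 score and location. Label the t-test and the model with socio-demographic and employment-history variables as supportive.
- **Reemployment.** Name one location-stratified comparison as primary, for example a Mantel-Haenszel risk difference. This matches the 10-percentage-point target in the Sample size section. It also avoids a logistic model with many sparse location terms: about 60 program runs and 900 analysed give 900/60 = 15 people per run on average. Keep the logistic models as supportive.
- **Covariate sentences.** Align the sentence on all multivariate analyses with the one on additional models. Do not delete it, because it is the only place that gives covariates for the logistic models of reemployment.
- **Main analyses.** State that the gender-stratified repeats and the t1 interim report use the named primary analysis.

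The cost is wording only. The t0 scores and location are already recorded, and the protocol's section on amendments provides the route for publishing a change to the statistical analyses.

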### Procedure

Due to the country-wide implementation of the JOBS Program Germany in the community-settings, the exact dates of enrollment and trainings will vary across the participating locations. Also, at some locations, more than one JOBS Program Germany will be conducted. However, for any given JOBS Program Germany at a given location, the time schedule is fixed.

Figure 1 shows the time schedule for a typical JOBS Program Germany at a given location. At each of the participating locations and for each JOBS Program Germany there will be an information event for the unemployed. This information event will be scheduled and announced (e.g., via flyer, by agents of the Jobcenters) about 4 to 5 weeks before the JOBS Program Germany starts (−*t*_*1*_). During these information events, two trainers, who will later lead the respective JOBS Program Germany, will explain the intervention and provide participants with a written information sheet that summarizes the objectives, procedure, and contents of the program. Trainers will also address any questions from potential participants. Participation is voluntary and free of charge, and a withdrawal is possible at any time without consequences. At the end of the information events, trainers will obtain written informed consent from the unemployed who are willing to participate.

Following the information event, participants who have given informed consent will be contacted and asked to complete an initial CATI during which participants’ eligibility for the trial is assessed. Participants meet the inclusion criteria if they are between 18 and 65 years old and currently unemployed according to the German Social Code, Book III by the time of the interview. Participants who, by the time of the interview, are full-time students or otherwise inactive on the labour market, and those with insufficient command of the German language to complete the CATI are excluded from the trial.

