#### Secondary outcome measures

The duration of unemployment, job-search intensity, and, if applicable, job satisfaction are collected via telephone interviews at all three occasions (*t*_*0*_, *t*_*1*_, *t*_*2*_, see Fig. 1). We measure job-search specific self-efficacy with a single Likert-type item that assess the likelihood of finding a job. At the baseline (*t*_*0*_), we also assess basic socio-demographic characteristics, such as participants’ age, gender, citizenship, and level of education.

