### Data collection and management

The first information events for recruiting participants will take place in March 2021 at four locations. While participants in these four locations follow the regular procedure and time schedule, as described above, the collected data will not be included in the (main) study and will not be part of the analyses. Instead, participants in these first four locations are treated as a pilot sample. This pilot sample will comprise approximately 50 participants who will be allocated to intervention and waiting control groups as described above. The main study is expected to start in April 2021. Participants in the pilot-study will complete JOBS Program Germany (if assigned to the intervention group), the post-test interview (*t*_*1*_), and the 6-months follow-up interview (*t*_*2*_), respectively (Fig. 1), about 1 to 2 months prior to participants of the main study. Questionnaires will be adjusted, if needed, within these 1 to 2 months before being administered to participants of the main study.

Questionnaires are developed by the research team at the University of Kassel, and implemented by SOKO in the CATI software Voxco. The implementation includes automated plausibility checks and filters. Interviews will be conducted by experienced interviewers, who will be trained to administer the specific questionnaires. Interviews will, on average, take 30 min to complete. A detailed methods and field report, including a description of quality assurance measures such as training and supervision of the interviewers, and data processing procedures will be compiled.

The Data will be collected and stored at SOKO, and handled in strict compliance with the German Federal Data Protection Act and the European General Data Protection Regulation (DSGVO). Participants’ contact information will be stored separately from the survey data (i.e., participants’ answers). After data collection, each respondent will be assigned a unique identification code, and the survey data (but not the contact information) will be transferred to the research team at the University of Kassel. Data transfer will be conducted via a secure data exchange server. The entire process of data collection, processing, storage, and backup will be documented in a detailed report.

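### Job satisfaction is assigned a baseline-adjusted, between-arm analysis, although participants must be unemployed at baseline and only the reemployed can have a value later

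*Protocol article*

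**What the plan says.** Four statements in the protocol article bear on this point.

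- *Procedure* admits only people who are "currently unemployed according to the German Social Code, Book III by the time of the interview". That interview is the t0 assessment, and allocation follows on its completion.
- *Secondary outcome measures* states: "The duration of unemployment, job-search intensity, and, if applicable, job satisfaction are collected via telephone interviews at all three occasions". The occasions listed are t0, t1 and t2.
- *Statistical methods* sets t-tests on scale outcomes and then: "In multivariate analyses, we will use linear regression models to adjust for baseline-measures of the respective outcomes". It extends this to job satisfaction by name: "We proceed in a similar fashion to analyze self-esteem, self-efficacy and our secondary outcomes job satisfaction and job-search intensity". No exception is stated.
- The same section applies intention-to-treat to all analyses: "Participants will be treated as belonging to the group to which they were originally (randomly) allocated". It uses complete cases up to 5% missing and continues: "If the proportion of missing values exceeds the predefined threshold of 5%, we will treat missing values by means of multiple imputation". It does not say whether a value that cannot exist, because the person has no job, counts as missing.

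**The concern.** The eligibility rule and the analysis rule do not fit together for this outcome. A model that adjusts for baseline job satisfaction needs a score from people who were enrolled because they had no job.

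The follow-up comparison has a different problem. Job satisfaction exists only for people who have found work, and finding work is a primary outcome that the programme is expected to raise. The employed in the two arms are therefore not comparable by randomisation. If the programme brings into work people who would otherwise have stayed unemployed, mean satisfaction among the employed can differ between arms without any effect on anyone's satisfaction, or a real effect can be hidden. The study calls itself confirmatory and labels all its analyses intention-to-treat, so such a difference could be reported as a randomised treatment effect when it is not one.

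**Working it through.** **The plan's own sample size.** Inputs from *Sample size*: d = 0.2, power 85%, two-sided alpha 0.05.

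n per group = 2 × (1.960 + 1.036)² / 0.2² = 2 × 8.98 / 0.04 ≈ 449. The plan states 450, so the figure reproduces. Power at 450 per group is 85.1%.

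For reemployment at 30% versus 40%, the required n is 407 per group (427 with continuity correction), and power at 450 is 88.3%. The statement that 450 suffices for this outcome also holds.

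**Baseline (t0).** By the eligibility rule, the share without a regular job is 100%. The only possible exceptions are people with the marginal or subsidised work mentioned under *Reintegration into the labor market*. The article gives no share for them and does not say whether they are asked about job satisfaction at t0. For everyone else:

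- If the absent t0 score counts as missing, it exceeds 5% and goes to multiple imputation, with practically no observed values from which to build an imputation model.
- If it does not count as missing, the covariate has no value and the participant cannot enter the adjusted model.

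On either reading the baseline-adjusted model is unusable for the trial population.

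**Follow-up (t2).** Inputs: 450 per group interviewed at t2 (Table 1), 30% reemployed in control, and a difference of 10 percentage points, hence 40% in the intervention group (*Sample size*).

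| | Control | Intervention | Total |
|---|---|---|---|
| Employed, outcome defined | 450 × 0.30 = 135 | 450 × 0.40 = 180 | 315 |
| No job, not applicable | 450 − 135 = 315 (70%) | 450 − 180 = 270 (60%) | 585 of 900 (65%) |

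If not-applicable values counted as missing, 65% would be 13 times the 5% threshold.

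**What a test among the employed could detect.** With d = 0.2 and no baseline term, the standard error of the standardised difference is √(1/135 + 1/180) = 0.114. Power ≈ Φ(0.2/0.114 − 1.96) = Φ(−0.20) ≈ 42%.

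Reemployment rates other than the plan's are assumptions:

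| Reemployment, control / intervention | Not applicable | Power for d = 0.2 |
|---|---|---|
| 20% / 30% (assumed) | 75% | 31% |
| 30% / 40% (plan) | 65% | 42% |
| 50% / 60% (assumed) | 45% | 60% |

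Low power is the lesser problem. The selection of the subset remains at any sample size.

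**The case against.** The best reply is that the article already treats job satisfaction as conditional. *Secondary outcome measures* collects it only where it applies, and *Data collection and management* says of the interview software: "The implementation includes automated plausibility checks and filters". Analysing in a similar way need not mean identically, which leaves room to drop a baseline term that does not exist. The unadjusted t-test can still be computed among the employed. Coding of filtered items is commonly left to an analysis plan, which is not shown.

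Part of this stands. A reader might infer that the plan will impute satisfaction scores for people without a job. The article does not say so: its rule concerns missing values, and the conditional collection and the filters point to a separate not-applicable code. Imputation is a reading the wording leaves open, not a stated step.

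A reader might also infer that duration of unemployment is a second unusable outcome, because it is listed under the secondary heading at all three occasions. The text does not support much of that. *Statistical methods* does say in general terms that secondary outcomes will be compared, but where it names them it lists only job satisfaction and job-search intensity. It uses duration as an adjustment variable and moderator, as Hypotheses 5 and 6 do. At most the heading is loose.

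The rest does not answer the point. The article itself names both the outcome and the method, so the mismatch is in the text shown. The t-test that remains possible is the comparison that conditions on reemployment, and nothing in the article marks it as different from the randomised comparisons.

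**Conclusion.** The point holds for one secondary outcome. The baseline-adjusted model for job satisfaction cannot be used as written, because its covariate is absent for essentially all participants by the eligibility rule. A few marginal-job holders may be exceptions, in a number the article does not give.

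At t2 the outcome is defined for about 315 of 900 people (135 versus 180). This figure rests on the plan's 30% and 40% reemployment and on Table 1's 450 per arm. A between-arm test in that subset is not an intention-to-treat comparison, whatever the actual rates turn out to be.

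The stronger claim, that the plan imputes job satisfaction for the jobless, goes beyond the text. The wording permits that reading for about 65% of t2 values but does not state it. No primary outcome and no sample-size figure is affected. Severity is minor.

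**What to change.** In *Statistical methods*:

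1. Exempt job satisfaction from the baseline-adjusted models.
2. State that a job-satisfaction value for a person without a job is not applicable rather than missing, and that such values neither count towards the 5% threshold nor are imputed.
3. Report job satisfaction descriptively by arm among those employed at t1 and t2, with the number employed in each arm alongside, and say that the comparison is not a randomised treatment effect.

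In *Secondary outcome measures*, align the listing of duration of unemployment with its use elsewhere as a covariate and moderator. No new outcome is needed.

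The cost is a few sentences, with no change to data collection or sample size. The price is that job satisfaction no longer supports a confirmatory statement. The planned data could not have supported one, given the selection and power of about 42% for d = 0.2.
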